### Study intervention platform

Each active intervention (CBT and social prescribing) will consist of eight one hour, weekly group based sessions delivered via telehealth. Each group will consist of 6–10 participants using a HIPAA-compliant zoom platform allowing group members to see and hear each other.

### CBT intervention

The aim of the CBT intervention is to develop skills and strategies to change unhelpful social cognitions and behaviors, increase overall participation in social contexts, and improve perceived quality in existing relationships. We will adapt our CBT intervention from Ehde’s chronic pain CBT protocol and Käll’s loneliness CBT protocol, given no established CBT protocol that addresses both long-term opioid use and loneliness in primary care patients exists [38, 39]. The CBT intervention will include education about the connections between loneliness and substance use, practice of behavioral skills for effectively managing chronic pain and activating social participation, teaching of how to identify, challenge and modify unhealth thoughts and beliefs about pain along with their replacement with helpful thoughts, and ways to address anxiety with social interactions. The weekly group sessions will be delivered by a study interventionist who is a behavioral health clinician, mimicking a behavioral health referral from clinic. Each session will include at least one in-group skill building exercise. After each session, participants will be provided with a session summary and suggested home practice worksheet to facilitate practice of skills between sessions.

### Social prescribing intervention

The aim of the social prescribing intervention is to reduce loneliness by increasing opportunities for social access and connection. This intervention is modeled from the United Kingdom National Health Services social prescribing services. The primary support for this will be a social navigator, who does not need to be a behavioral health trained personnel and can be a peer or community member. During the initial group, the navigator will work with participants to complete an inventory of the participants’ existing social network, former social network, and interests. Using this, in the second group, the navigator will work with the participants to develop an action plan to promote, establish or re-establish social connections. The action plan will be referenced and refined throughout the course of the 8 weeks. The navigator will facilitate focused discussions on barriers that may arise, such as social anxiety, and strategies to overcome them. In the final week, the navigator will collaborate with participants to create a sustainability plan.

### Usual care

Participants assigned to the usual care arm will be notified of their group assignment and told that they can continue receiving care or seek care as they usually would. They will also be given a one-page handout about loneliness and local resources. There is low risk of contamination since those in usual care will not be aware of patients in the other arms of the study.

### Effectiveness outcomes

The effectiveness outcomes will be assessed at baseline, at completion of the intervention (at 8 weeks) and at 3 months following the completion of the intervention.

#### Loneliness

Our primary outcome is loneliness, as measured by the UCLA loneliness scale, Version 3 [40]. This scale consists of 20 items that ask patients to identify “how often they feel” followed by a positive or negative description of social interactions and perceptions, with participants ranking the frequency as never, rarely, sometimes and always. The scale is scored from 20 to 80 with 80 being the most lonely, and 20 being the least.

#### Opioid misuse

Opioid misuse is our main secondary outcome, as described in our conceptual framework, and will be measured using the Current Opioid Misuse Measure (COMM) [41, 42]. The COMM is a self-administered questionnaire that assesses past 30 day behaviors concerning for addiction or taking a medication in a way other than how it is prescribed using 16 items each scored on a 5-point Likert scale with total scores ranging from 0 to 64. A COMM score of 13 or higher is indicative of problematic drug use and risk for opioid use disorder [43].

#### Secondary outcomes

Our other secondary outcomes include function [44], substance use [45, 46], social connection [47], depression [48], anxiety [49, 50], and prescribed opioid use. The measures for each outcome can be found in Table 1.

**Table 1 Tab1:** Effectiveness outcomes collected at baseline, post-intervention and 3 months post-intervention for randomized controlled trial

Outcome	Measure	Method of Collection
Loneliness	UCLA Loneliness Scale, Version 3	Patient report
Opioid Misuse	Current Opioid Misuse Measure	Patient report
Social Connection	Lubben Social Network Scale	Patient report
Substance Use	TAPS-1 (Tobacco, Alcohol, Prescription medication and other Substance use)	Patient report
Depression	PHQ-9	Patient report
Anxiety	GAD-7	Patient report
Physical Function	PROMIS physical functioning short form 6b	Patient report
Prescribed Opioid Use	Opioid type, dose and frequency (to calculate morphine equivalent dose)	EHR extraction

### Implementation outcomes

We propose using the RE-AIM (Reach, Effectiveness, Adoption, Implementation and Maintenance) framework to assess the feasibility of implementing a 3-arm trial [51, 52].

*Reach* – We will measure the proportion of patients who are reached and agree to participate in our study by tracking total patients reached and total patients enrolled. Specifically, we will track the demographic characteristics of gender, race/ethnicity, rurality and initial opioid dose to determine if specific subpopulations are more easily reached and enrolled in our study.

*Effectiveness* – see above for effectiveness outcomes.

*Adoption* – We will track the proportion of eligible clinics that agree to participate in the study and the number of eligible clinics that may be interested but decline to participate at this time. We will compare the clinic characteristics (size, rurality, patient demographics) of clinics that agreed to participate with those clinics that were eligible but declined participation. Furthermore, all study personnel who interact with participating clinics will keep notes on any interactions with clinic staff to measure level of engagement, which will be stratified by staff type, clinic type and patient population served.

*Implementation* – We will measure fidelity with both the CBT and social prescribing interventions. For the CBT intervention, the treatment fidelity protocol will consist of the level of adherence to the study manual with documentation from interventionists, fidelity checklist, and ongoing supervision meetings with the supervising investigators. We will also note any necessary adaptations that are made based on patients’ needs or expressed desires during the group sessions. Patients’ attendance and level of engagement in group sessions will also be documented by study interventionists. For the social prescribing intervention, we will track development of the patient narratives, network inventories and action plans, adherence to regular visits/check-ins with the social navigator, substantial variations in between patients in the intervention (i.e., visit durations, types of plans, etc.) and necessary adaptations based on patients’ needs or expressed desires.

*Maintenance* – We will measure if any change in outcomes at post-intervention is sustained at 3 months post-intervention for this trial. In a future pragmatic trial, we plan to measure sustainability at the practice/health system level.

### Qualitative interviews

Qualitative interviews will elucidate multiple elements from within the RE-AIM framework in greater detail. We will conduct 20 semi-structured interviews with patients (10 from the CBT intervention and 10 from the social prescribing intervention) at the conclusion of the intervention. We will recruit patients via phone with a $100 incentive offered to those who agree to and complete the interview (this incentive is in addition to other incentives offered to patients for completion of data measures). We will intentionally sample patients of diverse gender, race/ethnicity and geographic location, and if feasible, both patients who have attended the majority/all of the intervention sessions and those who have only attended a few (if any) of the sessions of the assigned intervention. We will ask patients about their experience of loneliness and how it has affected their chronic pain and opioid use, their experience of the interventions including any changes in their chronic pain, opioid use, and social connections that have occurred over the course of the treatment, history of opioid misuse and/or opioid use disorder (if any) and how this may have changed over the course of the interventions, thoughts about facilitators and barriers to accessing the intervention and suggestions for intervention improvements.

### Data collection

We will collect the outcome measures from patients in the week post intervention and 3 months post intervention (or for those in the usual care arm 10 weeks after initial data collection and then 3 months following that). Data collection will take place via phone, email or mail depending on the patient preference indicated in their baseline data collection. Patients will be given a $50 gift card incentive for each data collection time point.

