### Randomization

Prior to randomization, patients will be administered a baseline survey that includes a psychosis and cognitive screener, and demographic questions. After verification of eligibility, patients will be randomized using computer-generated random numbers to one of three groups: (1) CBT, (2) social prescribing or (3) usual care. There will be no stratification. The randomization will be blinded to the members of the study team responsible for data collection.

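### Usual care is followed up on a clock that starts at baseline and the active arms on one that starts when their course ends, so time since baseline can differ by arm in the primary comparison

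*Protocol article*

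**What the plan says.** The timing rules are spread over several sections of the protocol article.

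- **Data collection**, active arms: "We will collect the outcome measures from patients in the week post intervention and 3 months post intervention". The clock starts when the course ends, and no number of weeks from baseline is given.
- **Data collection**, usual care: "or for those in the usual care arm 10 weeks after initial data collection and then 3 months following that". The clock starts at baseline.
- **Effectiveness outcomes** gives one schedule without distinguishing arms: "at baseline, at completion of the intervention (at 8 weeks) and at 3 months following the completion of the intervention".
- **Study intervention platform** describes the course as "eight one hour, weekly group based sessions delivered via telehealth" and adds: "Each group will consist of 6–10 participants".
- **Randomization**: "Prior to randomization, patients will be administered a baseline survey". Any wait for a group therefore falls after baseline.
- **Quantitative analysis**: the linear mixed model contains arm, an indicator for the post-treatment time points, their interaction and a random intercept. It has no elapsed time and no covariates.

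**The concern.** Usual care has no course and no wait. Its first follow-up is fixed at 10 weeks from baseline. An active-arm participant is assessed after the wait for a group, the course, and up to a week for collection. How long after baseline a participant is measured is therefore set by a rule that depends on arm.

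Randomization balances the people in the arms. It does not balance a measurement date that the protocol sets by arm. If loneliness changes slowly over time without treatment, the arm measured later shows more of that change, and the model attributes the difference to the arm-by-post interaction, which is the primary estimate. The offset carries over to the 3-month visit and applies to every outcome assessed at these visits, including opioid misuse. Both active arms follow the same rule, so the CBT versus social prescribing comparison is largely unaffected.

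**Working it through.** **Plan's own figure.** With a difference of 6, SD 8.0, two-sided 0.05 and power 0.80 (Power analysis; sidedness from Quantitative analysis): n = 2 × (8 × (1.960 + 0.842) / 6)² = 27.9, so 28 per arm, as stated. The recruited 34 per arm is used as given. The sample size is not in dispute; it supplies the standard error and accrual count below.

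**Time from baseline to first follow-up.**

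- Usual care: 10 weeks.
- Active arms: W + course + collection lag, where W is the wait from baseline to the first session. Eight weekly sessions span 7 weeks from first to last, or 8 counted as full weeks. Collection adds 0 to 1 week. The total is W + 7 to W + 9.

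W is not in the article, so a range is shown:

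| Wait W (assumed) | Active arms, weeks from baseline | Difference from usual care |
|---|---|---|
| 0 | 7–9 | 3 to 1 weeks earlier |
| 1 | 8–10 | 2 weeks earlier to 0 |
| 2 | 9–11 | 1 week earlier to 1 later |
| 3 | 10–12 | 0 to 2 weeks later |
| 4 | 11–13 | 1 to 3 weeks later |
| 8 | 15–17 | 5 to 7 weeks later |

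With the course counted as 8 weeks, the clocks match when W = 10 − 8 − (0 to 1), that is 1 to 2 weeks.

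**Second follow-up.** Active: W + course + 3 months. Usual care: 10 weeks + 3 months. The 3 months cancel, so the offset is the same to within the collection lag.

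**Average wait under assumed accrual.** Assume that 34 per arm accrue evenly over M months, that groups have 8 members, and that a group starts as soon as it is full. The spacing between entrants is M × 4.345 / 34 weeks. The eight members wait 7, 6, …, 0 spacings, an average of 3.5. A bias in a mean depends on this average and not on the first member's wait, which is twice as long.

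Average gap = average wait + 8 + 0.5 − 10, with collection at mid-week. Bias = gap × drift, with an assumed drift of 0.1 to 0.2 points per week.

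| M (assumed) | Average wait | Average gap | Bias |
|---|---|---|---|
| 6 months | 3.5 × 0.767 = 2.7 weeks | 1.2 weeks | 0.1–0.2 points |
| 12 months | 3.5 × 1.534 = 5.4 weeks | 3.9 weeks | 0.4–0.8 points |
| 18 months | 3.5 × 2.300 = 8.0 weeks | 6.5 weeks | 0.7–1.3 points |

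Against the 6-point target this runs from about 2% (0.1/6) to about 22% (1.3/6).

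**Effect on the test.** For a simple comparison of two arms of 28, SE = 8 × √(2/28) = 2.14. With no true effect, a bias of 0.2 points gives a two-sided type I error of 0.051, 0.4 gives 0.054, 0.8 gives 0.066 and 1.0 gives 0.075, against a nominal 0.050.

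**The case against.** The 10 weeks may well be the sponsor's way of aligning the arms. Usual care has no course end, and a short start lag, eight weekly sessions and a collection week add up to about 10 weeks. If starts are prompt, the average gap could be near zero. The article does not say that participants are randomized singly and then queue, nor does it rule out enrolment in waves timed to group starts. The schedule figure is not shown. All of this stands, and it is why no definite bias can be claimed. What remains is that the alignment works only for one narrow range of waits, and nothing in the text holds the wait there.

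Some stronger readings are tempting, but the document does not support them:

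- **That 8 weeks and 10 weeks flatly contradict each other.** The 8 weeks in Effectiveness outcomes most naturally gives the length of the course, and Data collection then supplies the usual-care rule. The wording needs aligning, but it does not set 8 weeks for everyone.
- **That the bias favours treatment.** With no wait the active arms are measured earlier than usual care, and a natural decline would then count against them.
- **That regression to the mean after screening drives the bias.** Eligibility rests on the 3-item phone screen and the outcome is the separate 20-item scale. Regression due to screening error is shared by all randomized arms and does not grow with follow-up. Only slow change over time could differ between arms.
- **That loneliness is seasonal, or that waiting causes differential dropout.** Nothing in the document supports either.

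**Conclusion.** The point holds as a design weakness of uncertain size. Follow-up time depends on arm by a stated rule, the article states no limit on the wait that would keep the clocks together, and the primary model cannot separate elapsed time from arm. Confounding is therefore possible in both active-versus-usual-care contrasts, but it is not shown to be large or to run in a particular direction.

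The 0.1–1.3 points rest on three assumptions that the article does not supply: the accrual period, queuing until a group of 8 is full, and the drift rate. Shorter waits would shrink or reverse the figure; faster drift would enlarge it. The change is worth making because it is cheap, and because visits already held on different clocks cannot be realigned at analysis.

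**What to change.** 1. In Data collection, replace the fixed 10 weeks. Schedule each usual-care participant's two follow-ups in the same calendar weeks as the post-course and 3-month visits of the groups randomized concurrently. Fix the linking rule in advance, including what happens when the two active groups start in different weeks.
2. Make Effectiveness outcomes consistent with this, so that the 8 weeks is plainly the course length and not a visit time for all arms.
3. Record days from baseline to each visit for every participant, and report them by arm.
4. Add a sensitivity analysis of the primary model using actual elapsed time.

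**Cost.** Protocol wording and some scheduling work, since usual-care dates now depend on group start dates. No extra visits or patients are needed, and the sample size does not change.

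**Optional.** Randomizing in cohorts of about 18–30 (three arms of 6–10) would also align the clocks, but it is a real trade-off. At 102 patients over an assumed 12 months, a cohort of 24 takes 24/102 × 52 = about 12 weeks to fill, which delays randomization after baseline. The article describes no blocking, so a cohort of 18 would not be sure to yield 6 per arm without a blocked allocation scheme.

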### Power analysis

We plan to recruit 102 patients on long-term opioid therapy based on a sample size calculation allowing us to detect 6-point changes or more in the UCLA loneliness scale (Version 3). The 6-point change was determined by the mean loneliness score change from a previously published meta-analyses of psychological interventions for loneliness [31]. For the sample size calculation, we also assumed a significance level of 0.05, a desired power of 0.80, and a standard deviation of 8.0 (from weighted average from the original validation of the UCLA loneliness scale). Based on this, we will require 28 patients per arm. Assuming an 80% retention rate, we plan to recruit 34 patients per arm (or 102 patients total).

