### Hypothesis

We hypothesize that both CBT and social prescribing will be superior to usual care in reducing loneliness and that reductions in loneliness will then lead to reductions in opioid misuse. We hypothesize that CBT and social prescribing will be noninferior.

2)To assess implementation outcomes using the RE-AIM framework from a 3-arm randomized controlled trial testing the CBT and social prescribing interventions in primary care practices.

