### Quantitative analysis

The analysis population will include all randomized patients. Patients will be analyzed according to their assigned intervention group, regardless of what treatment they receive (intent to treat analysis). Descriptive statistics (mean and standard deviation) will be used to summarize the distribution of the primary outcome (loneliness), and secondary outcomes (opioid misuse, depression, anxiety, functionality and opioid dose) at baseline, immediately following the intervention and 3 months following the intervention. Linear mixed models will be used to test the association between the intervention arm and the change in the primary outcome and secondary outcomes across the study period. Since we expect that the effect from the intervention takes places immediately after implementation, we will include the intervention arm (control arm as the reference), an indicator for the post-treatment time points (immediately following the intervention and 3 months after) as well as their interaction as independent variables. Intervention assignment will be modeled as a fixed effect, and individual participants will be modeled as a random effect. Each model will contain a random intercept to account for the subject-specific correlation in outcome. In a secondary analysis, we will add a contrast variable to test the maintenance of outcomes between the second and third time points.

Subgroup analyses, which will be exploratory in nature, will be performed using the same modeling technique to assess the heterogeneity of treatment effects across subgroups of patients defined by age (grouped by tertiles), gender (male, female and nonbinary), rurality (rural urban continuum codes), initial opioid MME (calculated using the Centers for Disease Control and Prevention’s data file on opioid analgesic morphine milligram equivalents and grouped by tertiles) and initial loneliness score (grouped by tertiles).

Missing data mechanisms will be examined by correlating the proportion of missing data with key baseline characteristics. Multiple imputation by chained equations will be applied to account for loss-to-follow-up. Inferences will be drawn based on two-sided *p*-value of 0.05. Given that all participants are randomly assigned to one of the three intervention arms, we do not expect substantial bias in unadjusted analysis results. Hence, we do not plan to include control variables in our statistical modelling.

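### Dividing 28 per arm by 80% retention gives 35 per arm (105 in total), not 34 (102): a minor arithmetic slip worth about one percentage point of power

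*Protocol article*

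**What the plan says.** The Power analysis section sizes the trial to "detect 6-point changes or more in the UCLA loneliness scale (Version 3". Its other inputs are a significance level of 0.05, "a desired power of 0.80, and a standard deviation of 8.0". From these it concludes: "Based on this, we will require 28 patients per arm". It then allows for loss to follow-up: "Assuming an 80% retention rate, we plan to recruit 34 patients per arm (or 102 patients total". The power section does not say whether the test is one- or two-sided, but the Quantitative analysis section does: "Inferences will be drawn based on two-sided" p-values at 0.05. The Abstract repeats the total of 102.

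**The concern.** The section gives three linked figures: 28 required, 80% retained and 34 recruited. The third does not follow from the first two. Allowing for dropout means dividing the required number by the fraction retained. Adding 20% to the required number gives too few patients, because the 20% loss then applies to the larger, recruited number. The 28 has almost no slack, since the formula gives 27.9 before rounding up, so any shortfall takes the stated power below 80%. This is the article's only power statement, so its figures should agree with one another.

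**Working it through.** **Inputs.** Difference d = 6 points, SD s = 8.0, power 0.80, significance level 0.05, 80% retention, 28 required and 34 recruited per arm (all from Power analysis). Two-sided testing is from Quantitative analysis.

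**1. Reproduce the 28.** For two means by the normal approximation:

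n = 2 x (s/d)^2 x (1.960 + 0.8416)^2 = 2 x (8/6)^2 x 7.849 = 27.91, rounded up to 28.

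This matches the article. A one-sided test would give 22, so the 28 is a two-sided figure for one pairwise comparison.

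**2. Allow for 80% retention.**
- Dividing by the retained fraction: 28 / 0.80 = 35 per arm; 3 x 35 = 105 in total.
- Adding 20%: 28 x 1.2 = 33.6, rounded up to 34 per arm; 3 x 34 = 102 in total.

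The article's figures match the second line. That this was the method used is an inference.

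**3. Run the plan's figure forward.**
- Retained per arm: 34 x 0.80 = 27.2, against 28.
- Retained overall: 102 x 0.80 = 81.6, against 3 x 28 = 84.
- Retention needed to keep 28 of 34: 28 / 34 = 82.4%.

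**4. Power at the retained number.** The normal formula is power = Phi( d / (s x sqrt(2/n)) - 1.960 ). At n = 27 this is Phi(2.756 - 1.960) = Phi(0.796) = 78.7%.

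| Retained per arm | Normal approximation | Two-sample t-test |
|---|---|---|
| 27 | 78.7% | 77.2% |
| 27.2 | 79.0% | 77.5% |
| 28 | 80.1% | 78.7% |
| 29 | 81.5% | 80.1% |

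**5. Separate the slip from the choice of formula.** On the plan's own formula, the slip costs 80.1 - 79.0 = 1.1 points at 27.2 retained, or 80.1 - 78.7 = 1.4 points at 27. By t-test it costs 78.7 - 77.2 = 1.5 points at 27. The t-test is already 80 - 78.7 = 1.3 points short of 80% at a full 28. So about half of the t-test's 2.8-point gap (80 - 77.2) has nothing to do with retention.

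**6. Detectable difference at 80% power, normal formula.** With 27.2 retained: 2.8016 x 8 x sqrt(2/27.2) = 6.1 points, against the stated 6.

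**The case against.** The strongest reply is that 27 is a count of completers in a two-sample test at one time point, and that is not the planned analysis. The Quantitative analysis section includes all randomized patients in a random-intercept mixed model with a baseline and two post-treatment assessments, and imputes losses. The tested term is arm by post-treatment, which pools both follow-ups.

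The article gives no within-person correlation r, so a range has to be assumed. If 8.0 is a cross-sectional SD, as its source suggests ("a standard deviation of 8.0 (from weighted average from the original validation of the UCLA loneliness scale"), and r is the same between all visits, the variance of the mean of the two follow-ups minus baseline is 1.5 x (1 - r) x 64. With 27 completers per arm, the normal formula then gives:

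| Assumed r | 0.2 | 0.3 | 1/3 | 0.4 | 0.5 | 0.6 |
|---|---|---|---|---|---|---|
| Power | 71% | 77% | 79% | 83% | 89% | 94% |

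Above an r of roughly 0.35, power exceeds 80% even with 27. This part of the objection stands: the documents do not show that the planned analysis has less than 80% power. It does not rescue the sentence, however. The power section itself uses retention to reduce the usable number and claims no gain from repeated measures, and imputation does not replace information on patients who give no follow-up data.

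It is also fair to say that the normal approximation is conventional in planning. Using it is not an error, and the t-test's 29 is not a requirement of the plan.

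**Conclusion.** The arithmetic error is certain: the stated inputs give 35 per arm (105 in total), one more per arm and three more overall than planned. It is minor. Under the plan's own assumptions (6 points, SD 8.0, two-sided 0.05, one comparison with usual care, exactly 80% retention), power is about 79% rather than 80%. By t-test it is about 77%, but that method gives 78.7% even at 28.

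A reader might go further in three ways, none supported here.
- **That the trial is materially underpowered.** A loss of about one point does not show this, and the power of the planned mixed model could lie on either side of 80%.
- **That power should be judged on both interventions succeeding together.** The Hypothesis section says "We hypothesize that both CBT and social prescribing will be superior to usual care in reducing loneliness", but nowhere does the article make success depend on both comparisons being significant. Power per comparison is a normal basis for sizing a three-arm trial.
- **That clustering within therapy groups enlarges the shortfall.** The article gives no intraclass correlation, so no size can be put on this from the documents. In any case it is separate from the retention arithmetic.

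**What to change.** Correct the last sentence of Power analysis in one of two ways.

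1. Keep 34 per arm (102 in total) and state that, at 80% retention, about 27 per arm remain, giving about 79% power (normal approximation) for a 6-point difference in each pairwise comparison with usual care.
2. State 35 per arm (105 in total) as the size that matches 28 retained, and change the total in the Abstract to agree.

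The first costs one sentence and a slightly less favourable power figure. If the recruitment target is actually raised, the second also costs three more patients. Neither changes the design or the analysis. Whichever is chosen, name the formula used, so that normal-approximation and t-test figures are not mixed.
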